## **Objectives.** The purpose of this randomized controlled trial is to accomplish the following specific aims

**2**

Specific Aim 1: To quantitatively assess the effects of Isha yoga practices between seasoned practitioners and control groups on perceived stress, resilience, and wellbeing by use of validated scales.

Specific Aim 2: To compare protection and recovery from COVID-19 infection between seasoned Isha yoga practitioners and controls as demonstrated by:a.Self-reported duration of fever and respiratory symptoms in COVID-19 positive participantsb.Self-reported readiness to return to work (or a feeling of being physically and mentally fit)

Specific Aim 3: To compare prevalence rates of diagnosed COVID-19 infection between the seasoned Isha yoga practitioners and age and gender matched controls at baseline, 6 weeks and 12 weeks.

We hypothesize that routine yoga practice during the COVID-19 pandemic will reduce stress and enhance well-being.

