Aim 2 Analysis. To Compare Protection and Recovery from COVID 19 infection between seasoned Isha yoga practitioners and controls as demonstrated by:a.Self-reported duration of fever and respiratory symptoms in COVID-19 positive participantsb.Self-reported readiness to return to work (or a feeling of being physically and mentally fit)

We will calculate the protection and recovery rates from COVID-19 infection as defined by the aforementioned criteria. Given the continuous nature of the criteria used to assess symptom duration and sense of recovery, differences between groups will be assessed in a univariable manner with a parametric or non-parametric *t*-test. We will perform spot analysis at the three defined points to capture the point prevalence of recovery rates. We also intend to assess the differences between the prevention and recovery rates at baseline and six weeks and baseline and twelve weeks. We will employ the mixed model technique similarly to the analysis suggested in the aim #1 analysis.

Analysis of Aim 3: To compare Prevalence rates of diagnosed COVID-19 infection between the seasoned Isha yoga practitioners and age and gender matched controls at baseline, 6 weeks, and 12 weeks.

We will compute period prevalence of diagnosed COVID-19 infections as a measure of frequency. Since the data to be analyzed are not dependent on duration, we intend to compute the prevalence rates at the following time points: baseline, 6 weeks, and 12 weeks. The result would be reported as the portion of study population with COVID-19 at the specified time point.

Finally, we will perform an exploratory analysis of the data collected by comparing the effect of yoga practices and their duration between the 3 study groups to estimate a dose-response trend if possible.

Compliance is defined as 3 days of activity each week for at least 3 weeks from baseline to 6 weeks, or a minimum of 6 weeks from baseline to 12 weeks. Measures of frequency and association will also be calculated. We will complete exploratory analysis by comparing the different yoga practices and their duration between the 3 study groups to assess a dose-response pattern.

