We hypothesize that routine yoga practice during the COVID-19 pandemic will reduce stress, enhance well-being, and provide protective effects against COVID-19. While a direct comparison between seasoned yoga practitioners and non-meditators at baseline would have been sufficient to establish the effectiveness of yoga practices; the dynamic progression of COVID in varying geographical regions at different rates warranted these comparisons at least at two other time points separated by 6 weeks each. Furthermore, by incorporating a robust short (3 min) breathing yoga activity into the non-meditator cohort in a randomized fashion, we aimed to establish that exposure to any yoga practice will significantly improve mental health status in non-meditators. With the growing concern about the physical and mental impacts of COVID-19 and increased interest in alternative practices such as yogic techniques, this study will contribute to the growing body of evidence about the safety and efficacy of yoga for emotional, mental, and physical health conditions.

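### Aim 3 mixes period and point prevalence and on no reading isolates infections acquired during the study, so practitioners and controls can differ with identical in-study risk

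*Protocol article*

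**What the plan says.** Section 2 (Objectives) sets Aim 3 as follows: "To compare prevalence rates of diagnosed COVID-19 infection between the seasoned Isha yoga practitioners and age and gender matched controls". The comparison is to be made three times, once per survey round. Section 3.6 (Analysis) then defines the measure in three successive sentences:

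- It first names the measure: "We will compute period prevalence of diagnosed COVID-19 infections as a measure of frequency"
- It next gives the reason for that choice: "Since the data to be analyzed are not dependent on duration, we intend to compute the prevalence rates at the following time points" (the three survey rounds are then listed)
- It finally fixes how the finding will be expressed: "The result would be reported as the portion of study population with COVID-19 at the specified time point"

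The Discussion states the hypothesis behind the infection data: "We hypothesize that routine yoga practice during the COVID-19 pandemic will reduce stress, enhance well-being, and provide protective effects against COVID-19". It also says of the baseline contrast: "While a direct comparison between seasoned yoga practitioners and non-meditators at baseline would have been sufficient to establish the effectiveness of yoga practices".

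Three other places matter. Section 3.2 describes the practitioners as an observational arm; only the non-meditators are randomised. Table 1 lists no exclusion for earlier COVID-19. Section 3.3 says that surveys at all three time points carry questions on COVID-19 infection.

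**The concern.** Period prevalence and point prevalence have different numerators, and the text moves from one to the other without saying when the period begins. The stated reason does not hold either: at a given incidence, more people are ill on a given day if illness lasts longer.

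The larger matter is what the result could mean. Aim 3 is the article's only analysis of how often infection occurs, and the article hypothesises protection. Nothing in it restricts Aim 3 to new diagnoses, removes people already diagnosed from the denominator, or adjusts Aim 3 for infection at baseline. A difference that existed at enrolment, or a difference in illness duration, could then be reported as a lower frequency of COVID-19 among practitioners. The remark that a baseline contrast would have been enough to show effectiveness makes that misreading more likely.

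**Working it through.** The article gives no infection rate, event count or sample size, so there is no figure to reproduce. All rates and group sizes below are assumed. In-study risk is held equal in the two groups throughout.

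**What each reading counts**

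| Reading | What enters besides new infections |
|---|---|
| Baseline prevalence | Everything: only infections that began before or at enrolment can count |
| Period prevalence, period starting before enrolment | All earlier diagnoses within that period |
| Period prevalence, period starting at baseline | Cases still active at baseline |
| Point prevalence at 6 or 12 weeks | Duration: prevalence is roughly incidence rate × duration |

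**Point prevalence.** Assume a 5% risk over 84 days in both groups and illness lasting 10 v 14 days. Then 0.05/84 × 10 = 0.60% and 0.05/84 × 14 = 0.83%, a ratio of 10/14 = 0.71.

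**Period from baseline to 6 weeks.** Assume active cases at baseline of 1% v 2% and a 6-week risk of 2.5% in both. Then 0.01 + 0.99 × 0.025 = 3.475% and 0.02 + 0.98 × 0.025 = 4.45%, a ratio of 0.78.

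**Cumulative from before enrolment.** Prevalence at 12 weeks is b + (1 − b)r, with b the earlier-diagnosed fraction and r the common risk.

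- b = 2% v 4%, r = 5%: 6.9% v 8.8%, ratio 0.78.
- b = 2% v 6%, r = 5%: 6.9% v 10.7%, ratio 0.65.
- b = 5% v 5%, r = 5%: 9.75% in both, ratio 1.00. The gap comes only from unequal history.

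**How often this would reach p < 0.05.** Section 3.6 plans chi-square or Fisher's exact tests for categorical data. I enumerated all binomial outcomes and applied the uncorrected chi-square test at two-sided 0.05. Group sizes assume two controls per practitioner, with controls pooled as Aim 3 is worded. Prevalence is taken as history plus 4% new infections.

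| Practitioners v controls | 100 v 200 | 200 v 400 |
|---|---|---|
| 2 + 4 = 6% v 10 + 4 = 14% | 55% | 87% |
| 4 + 4 = 8% v 8 + 4 = 12% | 16% | 31% |

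Simple addition makes the risk among the previously undiagnosed only approximately equal (4/98 = 4.1% v 4/90 = 4.4% in the first row). Making it exactly 4% changes little:

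- 0.02 + 0.98 × 0.04 = 5.92% v 0.10 + 0.90 × 0.04 = 13.6% gives 53% and 85%.
- 0.04 + 0.96 × 0.04 = 7.84% v 0.08 + 0.92 × 0.04 = 11.68% gives 16% and 30%.

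With new diagnoses among the previously undiagnosed as the outcome, the comparison is r v r, the ratio is 1.00, and the test rejects at about its nominal 5%.

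**The case against.** Several points on the other side stand and limit the conclusion.

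- A reader might infer that the 6- and 12-week figures count every infection since before enrolment. The article does not say so. Taken literally, the final Aim 3 sentence drops resolved infections, and a period starting at baseline would add only cases still active then. The 55% and 87% therefore belong to one possible reading, and the wide assumed gap in history drives them.
- A reader might infer that the plan formally judges protection by Aim 3. Sections 2 and 3.6 attach that word to Aim 2, through symptom duration and readiness to return to work. The link from Aim 3 to the Discussion's hypothesis is reasonable but is not written down. Aim 3 is also neither the primary nor the key secondary outcome.
- A reader might treat all earlier infections as irrelevant to the practitioner comparison. Practitioners were already practising before enrolment, so some of those infections fell within exposed time and bear on a cross-sectional association. Confounding remains there, and switching to incidence does not remove it.
- A reader might extend the bias to Simha Kriya v reading or sitting idle. Randomisation balances earlier infection on average, so it costs precision only.
- Controls are approached after their practitioner enrols (section 3.1), so their surveys may fall later in the pandemic. No lag is given, so this is a reason to adjust, not a demonstrated bias.

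The Aim 2 comparison of baseline with follow-up does not repair Aim 3, because its rates are defined by symptoms and return to work, not by infection status.

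**Conclusion.** The concern holds in a limited form. Aim 3 conflates two measures, leaves the period without a start, and rests on a reason that is wrong for point prevalence and at odds with Aim 2. Whichever reading is chosen, new infections are not isolated, so the non-randomised practitioner–control comparison can show a difference with identical in-study risk. The randomised comparison is not systematically biased.

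The size cannot be determined from the article. On the assumed inputs, ratios of 0.65 to 0.78 appear where the true in-study ratio is 1, and the chance of a significant result runs from about 16% to 87% under the cumulative reading alone. The direction depends on which group has more earlier infection or longer illness, which the article does not tell us. This is worth correcting before any statement about protection, but it does not touch the primary outcome.

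**What to change.** Make the Aim 3 outcome newly diagnosed infection from baseline to 12 weeks among participants with no diagnosed infection at baseline. Report two results separately:

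- Simha Kriya v reading or sitting idle, as the randomised risk difference with 95% CI;
- practitioners v controls, as an observational association adjusted for location and enrolment date, stated not to establish protection.

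Report baseline prevalence as a descriptive characteristic only, and delete the duration rationale.

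Section 3.6 already records a move to three-group comparisons after the 12-week data were reviewed, so part of the separation exists. For the same reason, this change must be declared as made after data review and not presented as prespecified.

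No new data collection should be needed: infection questions are asked at all three surveys, so a first report after a negative baseline identifies a new diagnosis even if diagnosis dates, which the article does not mention, were not recorded. The cost is fewer events and wider intervals.

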### Participant recruitment

3.1

We will employ a two-stage recruitment design. First, seasoned yoga participants will be recruited by social media, websites, flyers, word of mouth, email announcements at the Isha Foundation [30], an international school of yoga. Seasoned yoga participants are defined as individuals who have completed at least one, in-person yoga Isha Yoga training protocol with an Isha yoga trainer and are regularly doing the practice. The Isha Foundation will facilitate this stage of the recruitment by including study recruitment flyers and links to its broad follower base of meditators and yoga practitioners. These communications will have a survey link where prospective participants can confirm their interest in the study and learn more detailed information about study procedures. They will then be directed to a brief REDCap survey where they will be asked screening questions to ensure study eligibility. Those who are eligible will be directed to an electronic consent form and enrolled in the study following the submission of the consent agreement.

The second stage of the recruitment uses snow-ball sampling [31]. Following enrollment in the study, seasoned yoga practitioners are requested to nominate two friends who can act as age and gender matched controls, preferably living in the same neighborhood. The study team will reach out to the nominated individuals to describe the study, assess interest and eligibility, and direct prospective respondents to an electronic consent form specific for the control groups. Respondents will be enrolled following the provision of their consent.

The process of nominating controls for the study is voluntary and seasoned yoga practitioners can participate without referring any controls. In this situation, unmatched controls and practitioners will be matched by the study team based on their self-reported location details. The team prioritizes matching the zip codes followed by town, city, county, and state.

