### Intervention description and timing

3.2

This is analytic study wherein an observational arm of ‘seasoned yoga practitioners’ is being compared with age, gender, and region matched ‘non-meditators’ as controls. The non-meditators control group is further randomized to active comparator arm and placebo comparator arm.

Control participants or Non-meditators are individuals with minimum (<1 month) to no yoga practice of any kind, prior to study enrollment. Non-meditator controls randomized to an ‘Active comparator arm’ are taught a 3 min yoga practice (Simha Kriya) which involves deep breathing exercises and meditation following randomization. Within the yogic tradition, there are breathing exercises which are considered to foster pranayama, which builds a type of “armor” or Kavacham for oneself against negative impacts encountered in the every day world. Prana is considered the fundamental energy and the foundation for all life. Pranayanic practices have been shown to contribute to positive physiologic and psychologic changes including improvements in hypertension, cognitive function, breathing frequency, stress, and heart rate variability [13,[32], [33], [34]]. In a study of another Isha pranayama practice, Peterson et al. found that after 6 weeks of daily practice, participants reported improved general well-being (General Well-Being Scale) and lower levels of perceived stress (Perceived Stress Scale) [35]. In the current study, the Simha Kriya practice will be taught on-line by highly-trained Isha practitioners and participants are asked to perform Simha Kriya using a web-based application, twice per day.

The other control group acts as a ‘Placebo comparator arm’ and performs either reading activities or remaining idle for 15 min a day throughout the study period. Respondents in the observational arm (seasoned yoga practitioners) continue their usual yoga practices. Please see Fig. 1 for study flow chart. Participants aged <18 years or >80 years will excluded from the study. Please see Table 1 for additional Inclusion/Exclusion Criteria.

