*Brief Resilience scale (BRS).* The BRS identifies an individual's ability to “bounce back” or recover from a stress. This 6-item scale is rated on a 5-point response scale (1 = Strongly disagree; 5 = Strongly agree). Responses from each of the 6 questions are summed to create a total score, producing a range of 6–30. The score is divided by the number of questions answered to calculate the individual brief resilience score.

*Warwick- Edinburgh Wellbeing Scale (WEMWBS).* The purpose of the WEMBS scale is to assess various aspects of mental health such as positive affect, satisfying interpersonal relationships, and positive functioning. This 14-item scale is rated on a 4-point response scale (1 = none of the time to 4 = all of the time). Response from each of the 6 questions is then summed to create a total wellbeing score.

*Post Traumatic Growth Inventory (PTGI).* The purpose of the PTGI is to capture the positive outcomes reported by a person who has experienced a traumatic event. This scale will be administered only to those participants who report being hospitalized during the COVID-19 pandemic. The scale helps to determine a respondent's coping ability in the aftermath of a trauma, their perceptions of self and others, and meaning of the event. This 21-item scale is rated on a 6-point Likert response scale and response to each question is summed to create a total PTGI score.

*Activity Diary.* The weekly activity diary is a tool which helps the participants to keep a track of their activities each week. This enables the study team to measure compliance and protocol adherence by the participants. Based on the construct of the study, we have 2 different activity diaries employed for data collection in this study. The activity diary for seasoned yoga practitioners collects information on their routine activity practiced, its frequency and duration. The activity diary for controls collects information on the activity suggested by study team (the Simha Kriya yoga practice vs placebo activity choices of reading or remaining idle).

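### The exploratory dose-response trend across the three study groups mixes amount of practice with self-selection and type of practice, so a trend in outcome levels can appear when practice has no effect

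*Protocol article*

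**What the plan says.** The Analysis section (3.6) of the protocol article states the dose-response analysis twice. The first statement, just after the Aim 3 analysis, is "comparing the effect of yoga practices and their duration between the 3 study groups to estimate a dose-response trend if possible". The second, after the definition of compliance, is "comparing the different yoga practices and their duration between the 3 study groups to assess a dose-response pattern". Both call the analysis exploratory, and both place the comparison between the three groups.

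The groups are formed in different ways. Section 3.2 describes a design in which "an observational arm of ‘seasoned yoga practitioners’ is being compared with age, gender, and region matched ‘non-meditators’ as controls". Section 3.1 defines seasoned participants as people who have "completed at least one, in-person yoga Isha Yoga training protocol with an Isha yoga trainer and are regularly doing the practice" and recruits them through the yoga school. Controls are "individuals with minimum (<1 month) to no yoga practice of any kind, prior to study enrollment". Randomisation applies to them alone: "The non-meditators control group is further randomized to active comparator arm and placebo comparator arm".

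The practices differ too. The active comparator does Simha Kriya, 3 minutes twice daily (3.5). The placebo comparator reads or stays idle. Practitioners must already practise one of two other kriyas (Table 1), and no dose is assigned to them: "Respondents in the observational arm (seasoned yoga practitioners) continue their usual yoga practices".

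On recording, section 3.4 says that the practitioners' diary captures the routine activity with its frequency and duration. For the other arms, "The activity diary for controls collects information on the activity suggested by study team".

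**The concern.** Three things change together along the proposed dose scale: the amount of practice, the kind of practice, and whether the person chose yoga before the study. With three groups, a between-group trend cannot pull these apart. The step from reading/idle to Simha Kriya is randomised. The step up to the practitioners is not, and that step dominates the slope.

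Matching on age, gender and location does not deal with the traits that lead someone to take up yoga and keep at it. Confounder adjustment appears under Aim 1, is optional, and depends on univariable screening; none is stated for the dose-response analysis.

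A dose-response pattern is commonly read as support for a causal effect. Here the same pattern could arise from selection alone and would largely restate the difference between practitioners and non-practitioners. The exploratory label warns that a finding is tentative; it does not remove confounding.

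**Working it through.** The article gives no sample size, SD, effect size or practitioner minutes, so there is no planned figure to reproduce. What follows is an illustration.

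**Inputs from the article**
- Two-sided significance level 0.05 (3.6).
- Simha Kriya 3 min twice daily, so 2 × 3 = 6 min/day (3.5).
- Reading/idle: 0 min/day of assigned yoga.

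**Assumptions**
- Equal groups of n = 50, 100 or 200, and outcome SD 1.
- No effect of any practice.
- Practitioners better by d = 0.2, 0.3 or 0.5 SD through selection alone.
- Practitioners at the top of the dose scale, coded either as scores 0/1/2 or as 0, 6 and 20, 30 or 40 min/day.

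**Formula.** For a linear trend on group doses x₁, x₂, x₃ with mean m, where only group 3 is shifted by d, the expected test statistic is about

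λ = d · √n · (x₃ − m) / √Σ(xᵢ − m)²

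and the rejection probability is Φ(λ − 1.96) + Φ(−λ − 1.96).

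**Numbers for n = 100 (√n = 10)**
- Scores 0/1/2: m = 1, Σ = 2, so λ = 10 × 1/1.414 × d = 7.07d.
- Doses 0/6/20: m = 8.67, Σ = 210.67, so λ = 10 × 11.33/14.51 × d = 7.81d.
- Doses 0/6/40: m = 15.33, Σ = 930.67, so λ = 10 × 24.67/30.51 × d = 8.09d.

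| Coding, n = 100 | d = 0.2 | d = 0.3 | d = 0.5 |
|---|---|---|---|
| 0/1/2 | 29% | 56% | 94% |
| 0/6/20 | 34% | 65% | 97% |
| 0/6/40 | 37% | 68% | 98% |

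Example: for 0/6/20 and d = 0.2, λ = 1.56 and Φ(1.56 − 1.96) is about 34%.

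**Sample size.** With scores 0/1/2, n = 50 gives 17%, 32% and 71%; n = 200 gives 52%, 85% and over 99%. Simulation with doses 0/6/30 (3,000 runs per setting) gives 21% to 81% at n = 50, 36% to 98% at n = 100 and 61% to 100% at n = 200.

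**Checks**
- With d = 0 the trend test rejects in about 5%.
- A t-test of the two randomised arms alone rejects in 4.4% to 5.4% whatever the shift in the practitioners.
- If the shift is the same at baseline and follow-up, the expected shift in change is d − d = 0. Simulation of the 0/6/30 trend on change scores, assuming a baseline to follow-up correlation of 0.6, rejects in about 5% at every n and d above.

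The inflation therefore belongs to trends in outcome levels. Change scores avoid it when the shift is stable, but they do not give a clean dose-response either. Practitioners were already practising at baseline, so their change over 12 weeks does not capture benefit gained earlier.

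**The case against.** The analysis is exploratory, and its first statement adds a condition of feasibility. It is neither the primary PSS analysis nor the key secondary analysis of the Brief Resilience Scale. The article does not say that the trend will support a causal claim. This stands and limits the severity.

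No model is specified. The wording could be read as estimating duration effects within each group and then comparing them, and section 3.6 elsewhere plans comparisons of change over time. This stands in part. Model form can be left to a fuller document, but the article itself twice places the contrast between the three groups. Individual diary minutes pooled across groups would still be dominated by the gap between practitioners and non-practitioners.

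The percentages measure the power to detect a shift that was assumed in the first place, and sample size drives them. This is fair: they show the mechanism and its possible size and are not forecasts for this trial.

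A reader might also infer that the control diary records nothing beyond the suggested activity, so that other yoga done by a control counts as zero dose. Section 3.4 does not say this. It states what the control diary collects, not that other practice goes unrecorded, and no rule for coding dose is given. The point does not need that inference.

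Finally, within-arm slopes are not causal either, because people choose how much they practise. This stands and shapes the fix.

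**Conclusion.** The concern holds for the three-group contrast as the article states it. Dose, self-selection and type of practice cannot be separated, and a trend in outcome levels can arise with no effect of practice. With an assumed 100 per group and a selection shift of 0.2 to 0.5 SD, a false trend appears in roughly 30% to 98% of trials instead of 5%. Sample size, shift and practitioner minutes are all assumed, and a stable shift would largely cancel in change scores.

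Two stronger readings are not supported. One is that the trial's primary result is compromised by this analysis: the dose-response analysis is exploratory, and the primary PSS analysis does not rest on it. The other is that every dose comparison in the trial is confounded: the Simha Kriya versus reading/idle step is randomised and free of self-selection into yoga. Severity is minor to moderate.

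**What to change.** - Do not report a trend across the three groups as dose-response.
- Use the randomised Simha Kriya versus reading/idle comparison as the only unconfounded contrast of practice against none.
- Where diary data allow, estimate the slope of change in PSS on recorded practice within the Simha Kriya arm, adjusted for baseline PSS, and separately within practitioners. The article names frequency and duration only for the practitioners' diary, so first confirm what the control diary holds.
- Report these slopes as associations: adherence is self-chosen, and the practitioners' baseline is already post-exposure.
- Label any three-group comparison that is kept as descriptive and confounded by self-selection and type of practice.

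Cost: the change is to analysis and reporting wording, with no new data collection. Within-arm slopes cover a narrower range of practice and are less precise. Section 3.6 says that amendments followed review of the 12-week data, so this change should be disclosed as made after data review.

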### Analysis

3.6

Baseline characteristics of participants will be recorded. Continuous data will be presented as means ± standard deviation or median (interquartile range) depending on the distribution of the data and assessed with a parametric paired *t*-test or non-parametric Wilcoxon signed rank test, as appropriate. Normality will be assessed with the Shapiro-Wilk test. Categorical data will be presented as frequencies and percentages and assessed with a chi-square or Fisher's exact test, as appropriate. All primary analyses will be assessed using intention-to-treat principles. SAS 9.4 (SAS Institute Inc., Cary, NC) will be used for all analyses with two-sided p-values < 0.05 considered statistically significant.

Aim 1 Analysis. To quantitatively assess the effects of Isha yoga practices between seasoned practitioners and the control groups on measures such as perceived stress, resilience, and overall wellbeing by use of validated scales at baseline, 6 weeks and 12 weeks. We have defined Perceived Stress Score as our primary outcome and Brief Resilience Scale scores as our key secondary outcome. Given the continuous nature of the scales used to assess stress, resilience and measures of well-being, differences between groups will be assessed with a parametric or non-parametric *t*-test. Multivariable regression may be utilized to adjust for potential confounders that deem to vary between the groups based on the univariable analysis prior to that. The distribution of the dependent variable will depend on the actual distribution of the scales recorded in the study. A mixed effect approach in modeling will address the similarity of the subjects enrolled in the study as friends or by matching, by assigning a random intercept to each cluster of related subjects. To assess whether there are differences between baseline and at six weeks, we will employ the use of paired t-tests or non-parametric tests for univariable analysis, as appropriate. Additionally, the change in scales over time can be compared between the groups using mixed models approach, wherein an indicator of time (baseline/6 weeks) will define the direction and significance of the change in a model, adjusted independent of other factors.

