After reviewing the data that was collected over the 12 week period, several amendments were made to the protocol. For example, we compared the three groups, Group 1: Simha-Kriya Yoga for a period of 12 weeks, Group 2: Reading activity/Sitting idle for a period of 12 weeks, and the Yoga Practitioners, rather than the combination of control groups with the yoga practitioners. We also performed Poisson regression rather than linear regression to account for potential confounders due to the distribution of the primary outcomes, PSS and BRS scores. These changes were towards a more conservative approach which we believe provided more valid inference.

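### The groups compared and the regression model were changed after the 12-week data were reviewed, so the three-group Poisson analyses are post hoc; BRS is labelled inconsistently and the claim that the changes are conservative is unsupported

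*Protocol article*

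**What the plan says.** All of this is in the protocol article.

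- **Outcomes.** Section 3.4 (Measures) names PSS as primary and BRS as key secondary. The Aim 1 text in section 3.6 repeats this: "We have defined Perceived Stress Score as our primary outcome and Brief Resilience Scale scores as our key secondary outcome".
- **Threshold.** Section 3.6 has "two-sided p-values < 0.05 considered statistically significant" and mentions no adjustment for multiple tests.
- **Model family.** The Aim 1 text leaves this open: "The distribution of the dependent variable will depend on the actual distribution of the scales recorded in the study".
- **Changes.** The closing paragraph of section 3.6 begins: "After reviewing the data that was collected over the 12 week period, several amendments were made to the protocol". Two instances follow. On the groups: "For example, we compared the three groups" (Simha Kriya, reading/idle, practitioners), "rather than the combination of control groups with the yoga practitioners". On the model: "We also performed Poisson regression rather than linear regression".
- **Reason given.** The model change is put down to confounder adjustment "due to the distribution of the primary outcomes, PSS and BRS scores". The article then describes the changes as moving in a conservative direction and as giving more valid inference, with no calculation.

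**The concern.** A significance test has its stated error rate only if the comparison and the model were fixed without knowledge of the results. Here the article itself says that both were altered after the data were reviewed. If the amended analysis is presented as the trial's main result, readers will take a data-informed choice for a planned one, and the assurance that the changes were conservative encourages them to do so.

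The BRS label matters for the same reason. One primary outcome and two primary outcomes are different claims about what the trial set out to show, and the article makes both.

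**Working it through.** The article gives no sample size, power, SD or overall error rate, so there is no figure of its own to reproduce. The one numeric design input is the two-sided 0.05. Everything else below is an assumption, shown as a range.

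**1. Number of contrasts at one visit**

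Before the change there is one contrast (practitioners versus combined controls) on one primary outcome, so the error rate is 0.05.

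After the change there are three groups, hence up to 3 × 2 / 2 = 3 pairwise contrasts. The article does not say that they are tested pairwise.

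Simple reference values, with each test at 0.05:
- 3 independent tests: 1 − 0.95³ = 0.143
- 6 independent tests (3 contrasts × 2 outcomes): 1 − 0.95⁶ = 0.265; upper bound 6 × 0.05 = 0.30

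Pairwise contrasts share groups, so these overstate the rate. A simulation under the global null (1,000,000 replicates, normal z-tests, PSS–BRS correlation 0 to 0.9, group-size ratios 1:1:1, 2:1:1 and 1:2:2) gives:

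| Tests at one visit | Chance of at least one false positive |
|---|---|
| 1 contrast, PSS | 0.05 |
| 3 pairwise, PSS | 0.12 |
| 3 pairwise, PSS and BRS | 0.17 to 0.23 (0.21 at correlation 0.5) |

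The group-size ratio makes almost no difference. If instead each of two groups is compared with one reference, the PSS rate is at most 2 × 0.05 = 0.10.

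**2. Is Poisson regression conservative?**

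Poisson regression sets the variance equal to the mean. If the true ratio is φ = variance / mean and no dispersion correction is made, a nominal 5% test has actual error 2 × [1 − Φ(1.96 / √φ)].

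| φ | Actual type I error |
|---|---|
| 0.5 | 0.006 |
| 1 | 0.05 |
| 2 | 0.17 |
| 3 | 0.26 |

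*PSS.* Assume means of 12 to 18 and SDs of 6 to 7. Mean 15, SD 6 gives φ = 36/15 = 2.4 and error 0.21. Mean 15, SD 7 gives φ = 49/15 = 3.27 and error 0.28. The extremes are φ = 36/18 = 2 (0.17) and φ = 49/12 = 4.08 (0.33). Under these assumptions uncorrected Poisson is anti-conservative for the primary outcome.

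*BRS.* Section 3.4 divides the item total by the number of items answered, so the score is a mean, not a count. With an assumed mean of 3.5 and SD of 0.7 to 0.8, φ is 0.49/3.5 = 0.14 to 0.64/3.5 = 0.18, and the test would almost never reject. The corresponding six-item total (assumed mean 21, SD 4.5) has φ = 20.25/21 = 0.96 and error 0.046. The p-value would therefore depend on whether the mean or the total is modelled, which is a sign that the family does not suit the score.

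**3. The outcome labels side by side**

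Section 3.4 and Aim 1 have PSS as primary and BRS as key secondary. The amendment paragraph has both as primary. The two changes it names are the groups and the regression; it names no outcome change.

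**The case against.** The strongest defence is that much of this was foreseen and all of it is disclosed. Aim 1 tied the distribution to the observed data and specified no linear model; linear regression is mentioned only in the amendment paragraph. Section 3.6 already planned a three-group comparison, and the Discussion gives the effect of a short practice in non-meditators as an aim. The article does not say that the review was done by group, and the reason offered for Poisson is the outcome distribution.

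Part of this stands. The choice of regression family is the milder of the two changes. But the planned three-group comparison was an exploratory look at dose-response, and the amendment paragraph says that the comparison it replaced used combined controls. A remark about distributions does not explain a change of groups. The article itself treats both as amendments made after data review.

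Several stronger readings are tempting and are not supported:

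- *BRS was promoted to primary after the data were seen.* The text does not list this as an amendment. It may be loose wording; what is documented is a contradiction.
- *Three unadjusted pairwise tests were carried out.* Neither pairwise testing nor the absence of adjustment is stated. A global test is possible, and an analysis plan that is not shown could contain an adjustment.
- *The inflation is far larger once visits are counted* (12 tests over weeks 6 and 12 would give 1 − 0.95¹² = 0.46 if independent). Baseline, 6 and 12 weeks were already in Aim 1, so that multiplicity does not come from the amendment, and the independence figure overstates it.
- *Nothing in the trial can be confirmatory.* The limitation attaches to the amended analyses, not automatically to a PSS analysis done as defined before the review.

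**Conclusion.** The point holds in this form. By the article's own account, the groups compared and the regression model were changed after the 12-week data were reviewed, so the three-group Poisson analyses are post hoc. The status of BRS is contradictory within the article and must be reconciled. The conservatism claim has no support. More contrasts raise the overall error rate, and Poisson regression may be anti-conservative for PSS while being very conservative for a BRS mean score.

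The size is conditional. With unadjusted pairwise testing, the false-positive chance at one visit goes from 5% to about 12% for PSS, or to about 17–23% if BRS counts as primary. The Poisson figures rest on assumed means and SDs and on no dispersion correction being made. None of these figures includes the effect of choosing the analysis after seeing data, which cannot be quantified from the article. That effect, more than the multiplicity, is why the amended results should not be called confirmatory.

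**What to change.** 1. Report the pre-review analysis in full (PSS as sole primary outcome, practitioners versus combined controls, linear model) beside the amended one.
2. Label the three-group Poisson analysis post hoc and not confirmatory.
3. Call BRS key secondary throughout, including in the amendment paragraph.
4. If pairwise contrasts are reported, adjust them, for example by Holm. The smallest p-value is then judged against 0.05/3 = 0.0167 for three contrasts, or 0.05/6 = 0.0083 for six.
5. Delete the statement that the changes are conservative.

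The randomised Simha Kriya versus reading/idle contrast may be highlighted on design grounds, but it must be labelled as chosen after data review. Making it the single primary contrast now would be another post-data choice, is not the comparison Aim 1 describes, and would not restore confirmatory status.

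The cost is one extra results table, some wording, and some p-values that may lose significance.
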